## Abstract

**Introduction:**

Stroke has a long-term impact on functional status and quality of life in multiple health domains. A well-coordinated managed care program for stroke patients is crucial for ameliorating patients’ health and cost-efficient use of resources. The aim of this study is the implementation and evaluation of an optimised cross-sectoral, coordinated and managed care program for stroke patients bridging secondary and tertiary care.

**Methods:**

In this multi-center mixed method sequentially controlled intervention study, stroke patients with ischemic stroke (I63), transient ischemic attack and related syndromes (G45), or intracerebral haermorrhage (I64) will be invited to participate. For a 12-months period, 235 consecutive patients are expected to be enrolled and assigned standard of care treatment as an active control group. During the following 12 months, 235 consecutive patients will be enrolled and assigned to a post stroke intervention program. The StroCare intervention consists of repeated outpatient visits with specialized stroke teams, the implementation of a case manager, the use of an electronical tool for communication between acute care, rehabilitation facilities, and out-patient care, and the definition of individualized treatment targets. Patients will be followed up for 24 months. The primary outcome is health-related quality of life measured by the Patient-Reported Outcomes Measurement Information System 10-Question Short Form (PROMIS-10) at 12 months after the index event, i.e. stroke or TIA. For the qualitative survey of the implementation process, 21 patients in the intervention group will be interviewed after implementation of the interventions. In addition, 20 health care providers and staff members will be interviewed before and after implementation. Additionally, economic outcomes will be evaluated after 6 and 12 months.

**Perspective:**

The study will not only provide information about the tested intervention but is likely to be helpful for clinicians, suppliers of reimbursement, and researchers in implementing and evaluating complex interventions in stroke care in general. With this program, the health care system will have a reference model at its disposal for transfer to other regions and settings.

**Trial registration:**

The trial is registered at ClinicalTrials.gov (NCT04159324). Approval of the local ethics committee (Ethik-Kommission der Ärztekammer Hamburg, Niedersachsen, Schleswig-Holstein) has been obtained.

## Introduction

Stroke is the most common cause of acquired long-term disability [1]. Many stroke patients have to live with a reduced functionality and changes in quality of life [2]. Increased life expectancy with a higher risk of stroke events and improved treatment interventions lead to more long-term survivors. After diagnosis and initial acute care, in general, inpatient or outpatient rehabilitative care follows in specialized clinics before long-term outpatient guidance by general physicians and neurologists. As a result, optimizing early steps towards rehabilitative care and detecting and preventing imminent recurrences at an early stage are becoming increasingly important in stroke care.

At present patients, the process of finding a place for neurorehabilitation and achieving treatment guarantee by the health insurance is often time consuming and leads to delay in the initiation of effective neurorehabilitative treatment [3].

Moreover, outpatient care after rehabilitation is largely insufficient [4]. Often, no medically experienced contact person is available for patients after rehabilitation [4]. This can lead to a compromised adherence to medication, insufficiently controlled risk factors and more frequent recurrent events. A lack of information of either the patients or their caregivers is one of the important reasons why follow-up treatments are not performed [4]. In up to 50% of the cases, the treatment goals regarding vascular risk factors are not met [5]. This represents a worldwide problem which was already by the World Health Organization WHO [6]. Complications needing treatment including repeated hospitalisations pose a strain for patients as well as for the healthcare system [7]. Furthermore, optimal stroke treatment depends on a multidisciplinary involvement and cooperation between in-patient clinics, general practitioners and physio- and occupational therapists, which is often lacking [4].

In order to improve stroke care in Germany, specific programs have been developed and are being tested. The program STROKE-OWL focuses on providing “stroke-guides”, similar to a case-manager (https://stroke-owl.de). The program SANO intends to build an integrated (intersectoral and interprofessional) network for stroke patients [8].

Stroke patients´ impairment to their quality of life can be measured by patient-reported outcomes (PROMs) and is associated with stroke severity and comorbidities(D. L. [9]). The EPOS approach comprised the implementation of the International Consortium for Health Outcome Measurement (ICHOM) Standard set for Stroke in clinical routine (David Leander [10]) and repeatedly assessed quality of life in follow ups at different time points after stroke [11].

## Methods

### Aim of the study

The aim of the present study is to evaluate cross-sectoral, coordinated and evidence-based stroke care (StroCare) in three hospitals and five rehabilitation centers, with three objectives: a) to assess the intervention effects on outcomes (effectiveness); b) to explore the implementation process; and c) to investigate economic outcomes.

### Study description and study design

The StroCare intervention will be evaluated in a multi-center mixed-methods sequentially controlled intervention study with a longitudinal design (Fig. 1). Onset is acute inpatient stroke treatment with subsequent neurological rehabilitation. Patients will be enrolled during their initial stay at the stroke unit for the control and intervention group during a 12 months period each, starting with the control group. Afterwards, the intervention will be deployed and enrolment in the intervention group will start. For individual patients, the intervention will cover a period of 24 months. The intervention effects on outcomes will be evaluated by a quantitative survey 12 and 24 months after stroke. In terms of the implementation process, qualitative interviews will be conducted with patients after the implementation of the interventions. Additionally, employees (doctors, nurses, and IT staff) involved in the study will be interviewed before and after the implementation of the interventions. Comparative analyses of health-care costs are planned 6 and 12 months after admission with admitted permission to insurance data files. Enrolment of patients in the control group started in January 2020. Scheduled duration of the entire study from first-patient-in to last-patient-out has been extended from 24 to 36 months due to the COVID-19 pandemic.

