### Data analysis

#### Analysis of effectiveness outcomes

The structural equality of the control and intervention groups at baseline will be examined to detect imbalances, using descriptive statistical analysis.

In order to evaluate the intervention effect on the two primary outcomes at the 12-months follow-up, data will be analyzed using linear mixed models. In the fixed part of the model, exposure to the intervention (StroCare vs usual care) will be included as the independent variable of interest. Potential confounding variables will be added as fixed effects in case of baseline imbalance, including demographic characteristics, stroke type and severity of stroke symptoms, as well as vascular and systemic features. The random effects part of the model will include variance parameters for the intercept and for the treatment effect across the participating clinics, respectively. Findings regarding the primary outcomes with an alpha error rate below 0.025 will be considered statistically significant (Bonferroni adjustment for two outcomes).

The primary outcome at the 24-months follow-up and the secondary outcomes will be analyzed using similarly structured models. In the case that data are not normally distributed, generalized mixed models will be applied. Findings regarding the secondary outcomes with an alpha error rate below 0.05 will be considered statistically significant.

Parameter estimates will be reported with 95% confidence intervals. Missing values will be handled using multiple imputation.

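### The stated 36 months from first patient in to last patient out is at least 12 months too short for the stated enrolment and 24-month follow-up

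*Protocol article*

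**What the plan says.** All statements are in the protocol article.

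- **Total duration** (Study description and study design): "Scheduled duration of the entire study from first-patient-in to last-patient-out has been extended from 24 to 36 months due to the COVID-19 pandemic".
- **Enrolment** (same section): stroke-unit patients are recruited "for the control and intervention group during a 12 months period each, starting with the control group". The order is then fixed: "Afterwards, the intervention will be deployed and enrolment in the intervention group will start". The abstract agrees that the second block follows the first: "During the following 12 months, 235 consecutive patients will be enrolled and assigned to a post stroke intervention program".
- **Follow-up** (abstract, Methods): "Patients will be followed up for 24 months". The design section and the effectiveness outcomes section both place surveys at 12 and 24 months.
- **Length of the intervention** (Study description and study design): "For individual patients, the intervention will cover a period of 24 months". The StroCare intervention section describes two years of nurse contacts.
- **Analysis** (Analysis of effectiveness outcomes): the primary comparison is at 12 months, and "The primary outcome at the 24-months follow-up and the secondary outcomes will be analyzed using similarly structured models". The same section says that missing values are multiply imputed and names no exception.
- **Enrolment time frame** (Sample size calculation): 24 months is the period in which the planned number of patients is to be recruited.

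**The concern.** The total duration has defined endpoints and is the current figure, after extension. The enrolment blocks are consecutive, so the last intervention patient enters no earlier than month 24 and has a 24-month assessment no earlier than month 48. A study that ends at month 36 does not reach it.

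The shortfall would not be shared between the arms. Controls enter first and complete 24 months inside the window; intervention patients enter second and do not. If 36 months were applied as written, the 24-month between-group model would compare an observed arm with an unobserved one, and the general imputation rule does not exclude filling in that arm. The primary outcome is also exposed, more mildly: it fits 36 months only if intervention enrolment starts the day control enrolment ends, although the design section places deployment between the two.

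**Working it through.** **Inputs.** Control enrolment 12 months and intervention enrolment 12 months, in that order (design section, abstract). Follow-up 24 months per patient (abstract). Primary time point 12 months (abstract, analysis section). 235 patients per group (abstract, sample size section). Deployment gap *g*: not given, so it is an assumption, shown for 0 to 3 months.

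**Formula.** Minimum duration = 12 + *g* + 12 + follow-up.

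**Step 1. Can the stated 36 months be reproduced?** With *g* = 0:

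| What must be completed | Sum | Months |
|---|---|---|
| Enrolment only | 12 + 12 | 24 |
| 12-month primary outcome in all patients | 12 + 12 + 12 | 36 |
| 24-month follow-up in all patients | 12 + 12 + 24 | 48 |

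The stated 24-month follow-up does not reproduce 36; the shortfall is 48 − 36 = 12 months. With *g* = 1 the need is 49 months, and with *g* = 3 it is 51.

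**Step 2. Who reaches month 24 by study month 36?**

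- Controls enter in months 0 to 12 and reach 24 months in study months 24 to 36. All fit.
- Intervention patients enter in months 12 to 24 and reach 24 months in study months 36 to 48. With *g* = 0, only a patient enrolled on the first day of that phase reaches it, exactly at the limit. With any gap, none does.

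**Step 3. Who reaches month 12 by study month 36?** Intervention patients reach it in study months 24 + *g* to 36 + *g*. With even accrual, 235/12 = 19.6 patients enter per month, so about 19.6 × *g* would fall outside:

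| Assumed gap *g* | Lost | Left of 235 |
|---|---|---|
| 0 months | 0 | 235 |
| 1 month | 20 | 215 |
| 3 months | 59 (25%) | 176 |

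These losses are conditional on the assumed gap and on month 36 being a hard stop.

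**Step 4. What might 36 months mean?** The pre-extension 24 months equals 12 + 12, the enrolment window alone, and matches the time frame in the sample size section. Read literally as last patient out, it would have ended the study before the intervention patients' 12-month assessments, which fall in months 24 to 36. This suggests that the duration sentence may describe recruitment. On that reading the 24-month visits come after month 36, the total runs up to about 36 + 24 = 60 months, and the 24-month comparison is feasible.

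**The case against.** A reader might infer that no 24-month outcome can exist in the intervention group and that the comparison is impossible. The article does not support that. It follows only if 36 months is binding and the follow-up statements are the ones in error. Step 4 points at least as strongly the other way: the simplest explanation may be a recruitment period with the wrong label. This objection stands.

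A reader might also infer a definite loss of primary-outcome data or power. That does not follow either. The article gives no length for deployment, the abstract has the second enrolment block following the first, and with no gap all 12-month outcomes fit. Only the conditional range in Step 3 can be stated.

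Nor does the article say that a wholly unobserved arm would be imputed. The rule is general, and a statistical analysis plan that is not shown may limit it. The affected comparison is also a later time point, not the primary one.

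None of this removes the inconsistency. If 36 months is total duration, it conflicts with the 24-month follow-up, measurement and analysis. If it is recruitment, the last-patient-out label is wrong, and the statements of 12 months per group and 24 months of enrolment no longer hold. The text needs correction on either reading, and no analysis plan can make 48 months fit into 36.

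**Conclusion.** The inconsistency is certain; its consequence for the data is not. The stated duration is at least 12 months shorter than the stated enrolment and follow-up require (36 against 48 months or more). This rests only on the article's own figures and consecutive enrolment.

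If 36 months is a binding end of study, 24-month data would be available for all controls (before dropout) and for essentially no intervention patient, and the planned 24-month model could not estimate a group difference from observed data. The 12-month primary outcome is not ruled out, but it has no margin: over an assumed deployment gap of 0 to 3 months, about 0 to 59 of 235 intervention patients would be lost. If 36 months is recruitment, neither loss follows and the error is one of labelling. The article does not decide between the two.

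**What to change.** State whether 36 months is recruitment or total duration, and reconcile the abstract, the design section, the sample size section, the StroCare intervention section, the effectiveness outcomes section and the analysis section.

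- **If it is recruitment:** correct the last-patient-out label, update the statements of 12 months per group and 24 months of enrolment, and give the true last-patient-out.
- **If it is total duration:** choose one of two courses.
  - Restate last patient out as at least 48 months plus deployment time.
  - Withdraw the 24-month between-group comparison, report 24-month control data descriptively, and state that 24-month values that could not have been observed are not imputed. The stated 24-month intervention and the two-year contact period would then also conflict with the study end, and the authors must reconcile them.
- **In either case:** state that follow-up stays open until the last intervention patient's 12-month PROMIS-10, and give the length of the deployment period. Show any loss of 12-month outcomes only as a range conditional on that length.

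Cost: wording, if 36 months is recruitment. If it is total duration and the 24-month comparison is kept, at least 12 further months of follow-up. If the comparison is withdrawn, no further data collection for it, but one planned analysis is lost and several sections need revision.

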**Fig. 1 Fig1:**
[figure not shown]
Exprected patient flow diagram for the assessment of effectiveness

### Eligibility criteria

Patients will be included according to the following criteria: treatment at one of the participating acute clinics, diagnosis (ICD-10) of ischemic attack (I63), transient ischemic attack and related syndromes (G45), intracerebral haemorrhage (I64), insurance with the BARMER health insurance agency, sufficient mastery of German language and written informed consent. BARMER insurance membership is necessary due to its cooperation to defray the follow-up examination costs and to give access to patient data. Exclusion is based on the following criteria: premorbid score of mRS≥4, present diagnosis of artificial respiration (Z99.1), dementia (F00.x., F01.x. or G30.x) or aphasia (R47), substantially impaired communication capacity due to aphasia or dementia and admission to a nursing home following the acute treatment.

Patients will be screened by study nurses via electronic health record for diagnosis and insurance company after admission to the stroke unit. They will not be involved in patients´ treatment.

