### Sample size calculation

In order to assess the effectiveness of the StroCare intervention, the two prospective groups will include all patients insured with the health insurance BARMER who will be hospitalised in one of the three participating clinics over a period of 24 months for stroke treatment and have given their written consent. Previous studies showed moderate to large effects of similar interventions on health-related quality of life with standardized mean differences (Cohen’s *d*) between treatment and control groups ranging from 0.2 to 0.6 [8, 12]. We aim to identify a moderate effect (Cohen’s *d*=0.3) of the intervention on patient’s experienced health-related quality of life. With a power of 80% and an alpha error of 0.025 (adjusted for two primary endpoints, the two subscales of the PROMIS-10), a sample size of *N*=213 patients per group (426 in total) will be needed. Accounting for an expected dropout rate of 10% results in a necessary sample size of 235 per group (470 in total). In the past few years, approximately 600 patients insured with BARMER with a diagnosis of stroke were treated annually in the three participating clinics. In the planned time frame of 24 months we thus expect to enroll the planned number of 426 patients if 39% of 1200 participants participate.

For the qualitative interviews it is indicated that on average 12 interviews are sufficient to reach theoretical saturation [13]. Thus, the planned sample size of a maximum of 21 patients enrolled in the intervention group and 20 employees of different departments (doctors, nurses, and IT staff) represents a meaningful basis for the investigation of the experience gained during the implementation.

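### The inclusion criterion labels ICD-10 code I64 as intracerebral haemorrhage, but that diagnosis is I61, so label and code define different populations

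*Protocol article*

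**What the plan says.** The criterion is stated twice in the protocol article.

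- **Eligibility criteria:** "diagnosis (ICD-10) of ischemic attack (I63), transient ischemic attack and related syndromes (G45), intracerebral haemorrhage (I64").
- **Abstract, Methods:** "stroke patients with ischemic stroke (I63), transient ischemic attack and related syndromes (G45), or intracerebral haermorrhage (I64").

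The Eligibility criteria section describes how candidates are found: "Patients will be screened by study nurses via electronic health record for diagnosis and insurance company after admission to the stroke unit". It does not say whether the nurses filter on codes or read the written diagnosis. The exclusions in the same section also carry ICD codes (Z99.1, F00.x, F01.x, G30.x, R47).

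The recruitment forecast under Sample size calculation rests on a count of past admissions: "approximately 600 patients insured with BARMER with a diagnosis of stroke were treated annually in the three participating clinics". The codes behind that count are not given.

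**The concern.** An inclusion criterion should let two people who apply it independently select the same patients. Here the words and the code point to different patients, and the mismatch appears in both places where the criterion is stated. A reader cannot tell whether the study population contains haemorrhage patients, unspecified strokes, or both.

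Two further effects are possible, but only under conditions the article does not establish:

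- The groups are enrolled one after the other, not randomised. If one clinic or enrolment period followed the code and another the label, case mix would differ between the groups being compared.
- Stroke type is a candidate adjustment variable if the groups are unbalanced at baseline. If that variable were built from the same code list, unspecified strokes would be recorded as haemorrhages.

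**Working it through.** The point turns on a comparison of text, not on a calculation.

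**Step 1: label against code.** The code meanings below are those of ICD-10, which the criterion names as its standard. The article does not reprint them.

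| Code listed | Label in abstract | Label in Eligibility criteria | Meaning in ICD-10 | Match? |
|---|---|---|---|---|
| I63 | ischaemic stroke | ischaemic attack | cerebral infarction | abstract yes; Eligibility criteria loosely worded |
| G45 | TIA and related syndromes | TIA and related syndromes | TIA and related syndromes | yes |
| I64 | intracerebral haemorrhage | intracerebral haemorrhage | stroke not specified as haemorrhage or infarction | no, in both places |
| I61 | not listed | not listed | intracerebral haemorrhage | absent |

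The I63 discrepancy is visible from the article alone: one code carries two labels. The I64 discrepancy needs the classification.

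**Step 2: who is eligible under each reading.**

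| Patient's coded diagnosis | Code followed | Label followed |
|---|---|---|
| I63, G45 | eligible | eligible |
| I61 | not eligible | eligible |
| I64 | eligible | not eligible as haemorrhage |

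The two readings agree on I63 and G45 and disagree on both I61 and I64.

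**Step 3: does the screening text settle it?** No. It says that nurses look in the electronic record for diagnosis and insurer, which fits either reading.

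**Step 4: does the sample size depend on it?** The inputs under Sample size calculation are d = 0.3, alpha = 0.025 and 80% power. Taking the test as two-sided:

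- Normal approximation: n = 2(z₀.₉₈₇₅ + z₀.₈₀)² / d² = 2(2.2414 + 0.8416)² / 0.09 = 211.2, so 212 per group.
- t-test: 212.48, so 213 per group, which is the stated figure.

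No term involves the diagnosis code. The required number and its power are the same under either reading.

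**Step 5: can the affected number be estimated?** No. The article gives no haemorrhage share among admissions or enrolled patients, and no count of I61 or I64 cases.

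**The case against.** The strongest reply is that the intended population is plain. The word haemorrhage is written out twice. The Sample size calculation section describes the groups as all consenting BARMER patients hospitalised at the three clinics for stroke treatment. A nurse who reads the written diagnosis would find haemorrhage patients as intended. The wrong code may then be a slip in a condensed article that never reached the screening list. One criterion also applies to both groups, so a shared labelling error would affect how the population is described, not the comparison. Finally, the code meanings are not printed in the article.

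Most of this stands as a limit on the consequences. It does not remove the error. A criterion that defines a diagnosis by ICD-10 can only be read with ICD-10, so looking up the code is part of applying the criterion and not reliance on an outside study.

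A reader might infer more than the article supports:

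- **That screening by code misses the haemorrhage patients.** No code filter is described.
- **That an insurer-data extraction would lose them.** The article plans to use insurance data with permission, but describes no selection of claims by an ICD list.
- **That the stroke-type variable is mislabelled.** Stroke type is not defined by code, and it enters the model only if there is baseline imbalance.
- **That case mix differs between the groups.** Nothing shows that clinics or periods read the criterion differently.

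**Conclusion.** The criterion is wrong as written. I64 and intracerebral haemorrhage are not the same diagnosis, and I61, the code for haemorrhage, is missing. The eligible population is therefore ambiguous in an operative part of the protocol.

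The finding goes no further than that ambiguity. Loss of haemorrhage patients is a possibility if the code was applied literally, not a demonstrated fact. The case-mix and adjustment effects are likewise conditional. No number of affected patients can be given, and the stated 213 per group and its power do not change.

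The verdict rests on one premise, the ICD-10 meanings of I61 and I64. It leaves open whether the error exists in the full protocol and the screening list or only in the article.

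**What to change.** 1. Reconcile label and code in the abstract and in Eligibility criteria: I61 if haemorrhage is meant.
2. State explicitly whether unspecified stroke (I64) is also eligible.
3. Use one label for I63 in both places. The abstract's wording, ischaemic stroke, avoids confusion with the TIA entry beside it.
4. State which codes, if any, were used for screening and for the count of about 600 patients a year.
5. If I64 was used as the screening code during control enrolment, which began in January 2020, check the existing diagnosis codes of enrolled patients and report I61 and I64 counts by group.

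Items 1 to 4 cost a text correction. Item 5 is needed only if the code was used, and is then a one-off check of existing records. The sample size calculation does not need to change for this point.
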